## Abstract

**Background:**

Many patients with Parkinson's disease (PD) lead a sedentary lifestyle. Promotion of physical activities may beneficially affect the clinical presentation of PD, and perhaps even modify the course of PD. However, because of physical and cognitive impairments, patients with PD require specific support to increase their level of physical activity.

**Methods:**

We developed the ParkFit Program: a PD-specific and multifaceted behavioral program to promote physical activity. The emphasis is on creating a behavioral change, using a combination of accepted behavioral motivation techniques. In addition, we designed a multicentre randomized clinical trial to investigate whether this ParkFit Program increases physical activity levels over two years in sedentary PD patients. We intended to include 700 sedentary patients. Primary endpoint is the time spent on physical activities per week, which will be measured every six months using an interview-based 7-day recall.

**Results:**

In total 3453 PD patients were invited to participate. Ultimately, 586 patients - with a mean (SD) age of 64.1 (7.6) years and disease duration of 5.3 (4.5) years - entered the study. Study participants were younger, had a shorter disease duration and were less sedentary compared with eligible PD patients not willing to participate.

**Discussion:**

The ParkFit trial is expected to yield important new evidence about behavioral interventions to promote physical activity in sedentary patients with PD. The results of the trial are expected in 2012.

**Trial registration:**

http://clinicaltrials.gov (nr NCT00748488).

## Background

Parkinson's disease (PD) is a progressive neurological disorder characterized by both motor symptoms (such as bradykinesia and postural instability) and non-motor symptoms (such as depression and cognitive impairment)[1]. Both motor and non-motor symptoms can result in reduced physical activity[2,3].

Observations in non-parkinsonian populations suggest that participating in regular physical activity has preventive effects (e.g. cardiovascular events, diabetes mellitus, dementia)[4-6] and positive symptomatic effects (on depression[7], sleep disturbances[8], health-related quality of life)[9]. Studies in PD patients concluded that brief physical therapy interventions can improve flexibility, balance and muscle strength[10,11]. In addition, preclinical evidence in animals with experimental parkinsonism raised the possibility that physical activity may directly alter the neurodegenerative process[12,13].

A critical question remains how PD patients can be stimulated best to achieve an enduring increase in their physical activities in daily life, in order to prevent co-morbid complications and to improve symptoms.

Simply informing subjects about the health benefits of physical activity is not enough to attain a sustained behavioral change. The challenges to induce a lasting change in exercise behavior are particularly great for neurological patients. To change lifestyle, behavioral programs should focus on appropriate supervision, social support from spouses and caregivers, and the individual's preferences and needs[14-16]. Achieving an enduring behavioral change also calls for specific strategies such as goal setting, problem-solving techniques and motivational interviewing[14,16,17]. Physical activity promoting programs including such elements were effective in sedentary people[15], patients with chronic heart failure[16], and patients with COPD[18].

Stimulated by these observations, we developed the ParkFit program: a multifaceted intervention to promote physical activity in sedentary patients with PD. In addition, we developed the ParkFit trial to investigate whether this program affords increased physical activity levels that persist for two years. The trial will also search for possible health benefits and risks of increased physical activity. Here, we describe the study design and baseline characteristics of this ParkFit trial.

## Methods

### Study Design

The ParkFit trial is a multicentre, randomized controlled trial comparing two arms: physical therapy with specific emphasis on promoting a physically active lifestyle (ParkFit Program); and matched physical therapy with specific emphasis on safety and quality of performing daily activities (ParkSafe Program) (Figure 1). Trial duration is two years. Full ethical approval has been granted for the study (CMO Regio Arnhem-Nijmegen). The study is registered at clinicaltrials.gov (nr NCT00748488).

**Figure 1 F1:**
[figure not shown]
**Design of the ParkFit study**.

### Patients

We started with all patients who visited their neurologist in 2007, 2008 or 2009 in 32 participating community hospitals. Eligibility criteria were: (a) PD, according to the UK Brain Bank Criteria[19]; (b) age between 40 and 75 years; (c) sedentary lifestyle defined as: < 3 times a week vigorous-intensity physical activity for < 60 minutes; or < 3 times a week moderate-intensity physical activity for < 150 minutes);[20] (d) Hoehn and Yahr ≤ 3. Exclusion criteria were: (a) unclear diagnosis (no gratifying and sustained response to dopaminergic therapy); (b) MMSE < 24); (c) unable to complete Dutch questionnaires; (d) severe co-morbidity interfering with daily functioning; (e) daily institutionalized care; and (f) deep brain surgery. Informed consent was obtained before the first assessment.

### The Intervention

After baseline assessment, patients were randomly assigned to the ParkFit or ParkSafe Program. In both groups, patients receive high quality physical therapy: both interventions are delivered exclusively by experienced therapists who participate in the Dutch ParkinsonNet[21,22]. Patients in both treatment arms are offered an equal maximum number of treatment sessions (i.e. 35 sessions of 30 minutes a year; Table 1). Therapists contact patients at least every six months to investigate if there are new aims.

**Table 1 T1:** The ParkFit and the ParkSafe program

	ParkFit	ParkSafe
**Intensity** **Year 1**	Maximum of 19 physical therapy sessions based on problems and disabilities as perceived by each individual patient; the systematic way of tailoring goals is described in the evidence-based guideline for physical therapy in PD	Maximum of 35 physical therapy sessions based on problems and disabilities as perceived by each individual patient; the systematic way of tailoring goals is described in the evidence-based guideline for physical therapy in PD
	16 coaching sessions to identify and focus on individual beliefs and aims to promote a physically active lifestyle	
**Intensity** **Year 2**	Maximum of 23 physical therapy sessions based on problems and disabilities as perceived by each individual patient	Maximum of 35 physical therapy sessions based on problems and disabilities as perceived by each individual patient
	12 coaching sessions to identify and focus on individual beliefs and aims to promote a physically active lifestyle	
**Specific Elements**	ParkFit Brochure: • *Education about benefits of physical therapy* • *Identifying aims of physical therapy* • *Education about the benefits of physical activity* • *Identifying barriers to engage physical activity* • *Setting goals* • *Recruiting social support* • *Sign a health contract to support patients in initiating and maintaining* *physical activities* • *A logbook to describe and monitor the specific goals*	ParkSafe Brochure: • *Education about benefits of physical therapy* • *Identifying aims of physical therapy* • *Education about the importance of safety when performing* *daily activities*
	Physical therapist: who treat the patient in order to obtain the aims of the individual projected treatment plan Personal Activity Coach: who guide patients towards a more active lifestyle	Physical therapist: who treat the patient in order to obtain the aims of the individual projected treatment plan
	Goal setting: creating goals to increase the level of physical activity in order to obtain the half- year-goals as formulated in the health contract; goals will be evaluated as well as experienced barriers and possible solving techniques	
	Ambulatory Activity Monitor: gives visual feedback about the level of physical activity during the day	
	Bi-annual newsletter: specific information about physical activity, general information about Parkinson's disease, and general entertainment in order to facilitate compliance	Bi-annual newsletter: specific information about physical therapy, general information about Parkinson's disease, and general entertainment in order to facilitate compliance

#### ParkFit Program

Widely used behavioral change techniques, with demonstrated effectiveness[16,18] and based on models of behavioral change[14,17], are combined in the ParkFit Program to stimulate patients to increase their physical activity levels.

##### 1) Brochure ParkFit

Patients receive a brochure covering specific strategies to promote a behavioral change. These strategies include: education about the benefits of physical activity, advice about suitable activities, identifying and overcoming any perceived barriers to engage in physical activity, setting goals, and recruiting social support[14,23,24]. Part of the educational workbook is a health contract: a written agreement signed by the patient and physiotherapist to support them in initiating and maintaining physical activities[25]. A logbook monitors the specific goals.

##### 2) Personal Activity Coach

Physical therapists serve as personal activity coaches who guide patients towards a more active lifestyle, during specific coaching sessions. Their task is to educate patients about the beneficial effects of physical activity. Patients are additionally stimulated to participate in group exercise to experience the beneficial effects of physical activity and to receive social support from fellow patients[26]. For safety reasons, all patients are encouraged to receive a preventive sports medical screening.

##### 3) Goal setting

Patient and coach create activity goals in order to obtain the 6-month-goals (as formulated in the health contract). Goals have to be realistic, concrete and individualized and have to be formulated in a systematic way, based on behavioral change theories[25].

##### 4) Ambulatory Activity Monitor with visual feedback

Patients receive a personal ambulatory monitor with automated visual feedback showing the amount of actually delivered daily physical activity, recorded by a triaxial accelerometer[27,28]. Additionally, a personalized website shows the activity history[27]. Previous work showed that feedback from pedometers increases physical activity levels in COPD patients[29], sedentary workers[30] and patients with diabetes mellitus[31].

##### 5) Physical therapy

The ParkFit Program also includes a maximum of 19 physical therapy sessions in year 1 and 23 in year 2. Based on individual disabilities, therapist and patient jointly formulate treatment aims based on the evidence-based guideline of physical therapy for PD[32].

#### ParkSafe Program

The ParkSafe Program includes physical therapy interventions from the physical therapy guideline for PD[32] to stimulate patients to move more safely, e.g. by improving the quality of transfers, but without explicit emphasis on reaching a physically active lifestyle.

##### 1) Brochure ParkSafe

Patients receive a brochure with information about the benefits of physical therapy[32]. Specific emphasis is given to the importance of safety when performing daily activities.

##### 2) *Physical therapy*

Patients receive an individualized physical therapy program. We maximized the total number of sessions at 35/year, to avoid large differences in number of treatment sessions between the two arms (patients in the ParkFit arm also receive 35 annual sessions: 19 physiotherapy plus 16 coach sessions). 35 sessions is considered sufficient for patients in Hoehn and Yahr stage ≤ 3. Physical therapist and patient jointly formulate the aims of the projected treatment plan, based on individual problems and disabilities. The aims of the physical therapy sessions in both treatment arms are derived from the guideline for physical therapy in PD.

### Implementation

#### Training for physical therapists

All participating physical therapists were specifically trained to treat patients in both treatment arms and informed about the aim of the study. Special attention was given to models of behavioral change,[14,17] to specific strategies of coaching sedentary patients,[15,33] and to the technique of setting realistic, concrete and individualized goals[25]. Throughout the trial, therapists continuously register the individual treatment sessions.

### Outcome measures

#### Baseline characteristics

Blood pressure, height, body weight, education and employment are assessed at baseline as well as alcohol use, smoking history and lifetime physical activity[34]. Participants in the ParkFit Program also completed a questionnaire about attitude, social support and self-efficacy towards physical activity.

#### Primary endpoint: level of physical activity

Primary endpoint is the level of physical activity, as measured with a 7-day recall, based on an interview-based physical activity questionnaire, the LAPAQ[35]. Patients are asked to list their daily amount of activity (frequency and duration), so total time spent on physical activity (in hours per day) will be calculated. A MET-value will be used to calculate the number of kilocalories spent per day per kilogram of body weight[36]. The LAPAQ is completed during a face-to-face interview (at baseline, 12 and 24 months) and at additional time points by telephone (6 and 18 months). We assume that patients will increase their level of physical activity during the first months of intervention and then maintain this level. Therefore, main endpoint is the level of physical activity during the entire follow-up period (i.e. the mean of 6, 12, 18 and 24 months).

#### Secondary endpoints (Table 2)

**Table 2 T2:** An overview of patient assessments

	Baseline	6 months	12 months	18 months	24 months
	*Visit &* *Questionnaires*	*Questionnaires*	*Visit &* *Questionnaires*	*Questionnaires*	*Visit &* *Questionnaires*
**Physical Activity**					
*LAPAQ*	x	x	x	x	x
*Activity Monitor*	x	x	x	x	x
*Activity Diary*	x	x	x	x	x
**Physical Fitness**					
*6 MWT*	x		x		x
*Åstrand-Ryhming test*	x		x		x
**Quality of Life**					
*PDQ-39*	x	x	x	x	x
**Health Effects**					
*UPDRS III, motor function*	x		x		x
*Nine hole peg board test*	x		x		x
*Timed up and go test*	x		x		x
*DXA*	x				
*SCOPA-sleep*	x	x	x	x	x
*HADS*	x	x	x	x	x
*FSS*	x	x	x	x	x
*Cognitive testing battery**	x		x		x
*PD medication*	x	x	x	x	x
*Medical costs & EQ-5D*	x	x	x	x	x
*Number of falls (monthly)*	x	x	x	x	x
**Determinants**					
*Blood pressure*	x		x		x
*Height*	x		x		x
*Body weight*	x		x		x
*Education*	x				
*Employment*	x				
*Alcohol use*	x		x		x
*Smoking*	x		x		x
*Lifetime physical activity*	x				
*Attitude, SS & SE***	x				

** Including tests for spatial working memory*[49], *intra- and extra-dimensional shift performance*[50,51], *paired associate learning performance*[50], *phonemic and semantic word fluency*[52], *and complex figure drawing*[53]

** Only patients in the ParkFit Program

Secondary measures include: (a) physical fitness, measured with the six minute walk test (6MWT)[37]; (b) quality of life, measured with the PDQ-39[38]; and (c) level of physical activity in time and kilocalories per week, measured with the same tri-axial accelerometer that is used as feedback-tool in the ParkFit Program[28]. The level of physical activity is additionally measured with a physical activity diary.

#### Additional measures

Patients who increased their amount of physical activity will be compared with patients unable to achieve this, to assess specific health consequences. Disease progression (UPDRS motor section [39]; 9-hole peg board test[40]), mobility (Timed Up and Go test[41]), quality of sleep (SCOPA-sleep[42]), anxiety and depression (HADS[43]), fatigue (Fatigue Severity Scale[44]), and cognitive functioning (Table 2 for test battery) are assessed. Additionally, physical fitness is measured with the Åstrand-Ryhming test[45]. Bone mineral density (dual energy X-ray absorptiometry, DXA) is determined in a subgroup of 300 patients. PD medication and medical costs (combined with the EQ-5D[46]) are assessed, as well as the number of falls (as an index of safety). Patients are asked whether their falls occurred during exercise and about the consequences of falls (e.g. injuries). Information about other adverse events is collected systematically at each physical assessment.

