#### Statistical analyses

All participants who really started with their program, will be included in the primary analysis. The results after 6, 12, 18 and 24 months will be evaluated using a linear mixed model with random nested factors 'patient' and 'exercise group'. Fixed factors will be treatment arm, LAPAQ score at baseline, month, month*treatment (interaction), and the factors region, H&Y stage, age, gender and bone density assessment. In an additional analysis, the influence of H&Y stage, age, gender and level of previous sports activities on the success of the treatment will be evaluated by including the interaction terms between treatment and each of these variables in the model. Multiple imputation analyses will be used to evaluate the impact of missing values on the outcome. Throughout, 95% confidence intervals will be calculated.

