## Results

### Inclusion procedure

Selection of patients ran from September 2008 to January 2010. A total number of 4479 patients received a screening questionnaire; 587 (13.1%) did not respond, 439 (9.8%) were excluded because there was doubt about the diagnosis (Figure 2). After invitation for participation, 1766 patients were excluded based on our exclusion criteria, and 1101 eligible patients were excluded because they were not willing to participate. Finally, 586 patients signed informed consent. The number of enrolled patients is less than the power calculation required. However, the power remains over 80% because only 60% of patients participates in exercise groups with an average group size of only three, whereas our power calculation assumed that all patients would participate in exercise in groups of eight patients.

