The endpoints of this trial cover several complementary domains. A prerequisite is that patients will actually increase their physical activity levels. To document this, we have selected the time spent on physical activities per week as primary endpoint. We choose the LAPAQ as primary outcome measure instead of the Activity Monitor because a questionnaire covers a wider range of activities[48].

We also want to see whether physical activity affords any symptomatic relief of PD. To this end we have included a battery of additional endpoints (including quality of life) that measure possible health benefits for patients. Safety is also an issue, because physical activity may theoretically predispose patients to falls. Therefore, this will also be documented in this study. Furthermore, costs will be recorded, although we have no specific a priori reason to expect drastic increases or reductions in costs associated with the interventions of this trial.

In conclusion, the ParkFit trial is expected to yield important new knowledge about behavioral interventions for patients with PD to change their sedentary lifestyle. If the ParkFit Program shows good treatment compliance and beneficial symptomatic effects, future trials could identify which components of our multifaceted approach are most effective. In addition, positive results may have implications for different neurological disorders where beneficial effects of physical activity may be expected. The results of the ParkFit trial are scheduled for 2012.

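### The health consequences of activity are to be assessed by comparing patients who increased their activity with those who could not, a post-randomisation grouping that can show a benefit where there is none

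*Protocol article*

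**What the plan says.** The Additional measures section of the protocol article opens with the comparison it intends: "Patients who increased their amount of physical activity will be compared with patients unable to achieve this, to assess specific health consequences". It then lists motor progression (UPDRS motor section, peg board), Timed Up and Go, sleep, anxiety and depression, fatigue, cognition and the Åstrand-Ryhming fitness test. Bone density in a subgroup, medication, costs and falls come after these. Falls enter with the words "as well as the number of falls (as an index of safety".

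The purpose is put in causal terms. The Background says "The trial will also search for possible health benefits and risks of increased physical activity", and the Discussion says "We also want to see whether physical activity affords any symptomatic relief of PD". The Background also states: "Both motor and non-motor symptoms can result in reduced physical activity".

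The Statistical analyses section describes one linear mixed model: "Fixed factors will be treatment arm, LAPAQ score at baseline, month, month*treatment (interaction", plus the stratifying and clinical factors. Because baseline LAPAQ is a covariate, this is the model for the primary endpoint. The article gives no definition of an increase, no adjustment and no cautionary label for the increaser comparison.

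**The concern.** Randomisation balances prognosis between ParkFit and ParkSafe. It does not balance prognosis between patients who did and did not become more active. Someone whose disease progresses slowly, whose mood holds up or who is less fatigued finds it easier to be active. The listed outcomes are therefore possible causes of group membership as well as possible consequences of activity. The article supplies this mechanism in its own Background, and by describing the comparison group as unable to increase it points to impairment as a reason for being in that group.

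At stake is the trial's second question, whether activity brings health benefits or risks. Answered by this contrast, the question loses the protection of randomisation, and a difference in prognosis could be reported as an effect of activity. A larger sample does not help: it makes a biased difference more likely to reach significance.

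**Working it through.** The article gives no figure for this comparison, so there is none to reproduce. The check asks how often the contrast would favour increasers if activity had no effect on health.

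**Inputs from the article**
- Patients: 586 (Inclusion procedure: "Finally, 586 patients signed informed consent").
- Expected drop-out: 10% (Sample size calculation), so 586 × 0.9 = 527 analysable.
- Two-sided 95% confidence intervals (Sample size calculation), so a critical value of 1.96.

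**Assumptions, because the article gives neither**
- ρ, the correlation between change in activity and change in health that arises only from shared prognosis: 0 to 0.30.
- p, the share of patients who count as increasers: 0.5, with 0.3 as a check.

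**Formulas** (outcome in SD units, no covariate adjustment, since none is stated)
- Spurious difference: d = ρ × φ(z_p) × [1/p + 1/(1−p)], where φ is the normal density at the cut-point.
- Standard error: SE = √[1/(527p) + 1/(527(1−p))].
- Chance of a significant result in favour of increasers: 1 − Φ(1.96 − d/SE).

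**Worked case, ρ = 0.20 and p = 0.5**
- d = 0.20 × 0.399 × 4 = 0.319 SD.
- SE = √(1/263.5 + 1/263.5) = 0.0871.
- d/SE = 3.66, and 1 − Φ(1.96 − 3.66) = 0.956.

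**Range**

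| ρ | d, p = 0.5 | False benefit, p = 0.5 | d, p = 0.3 | False benefit, p = 0.3 |
|---|---|---|---|---|
| 0 | 0 | 2.5% | 0 | 2.5% |
| 0.05 | 0.080 | 14.8% | 0.083 | 13.8% |
| 0.10 | 0.160 | 44.9% | 0.166 | 41.4% |
| 0.20 | 0.319 | 95.6% | 0.331 | 93.6% |
| 0.30 | 0.479 | over 99% | 0.497 | over 99% |

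The nominal rate in the favourable direction is 2.5%.

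**Simulation check.** Activity change and health change shared a latent prognosis, with no effect of activity on health (4,000 runs per setting, 527 patients). For p = 0.3 and p = 0.5, the false-benefit rate was 35% and 39% at ρ = 0.09, 80% and 83% at ρ = 0.16, and over 99% for both at ρ = 0.25. This agrees with the formula.

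**Same data by randomised arm.** The mean difference was 0.00 SD and the two-sided rejection rate lay between 4.6% and 5.6% in every setting.

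**The case against.** The best defence is that these are third-tier measures in a condensed article, that the stated aim is only to search for possible benefits and risks, and that models for each measure normally sit in an analysis plan that is not shown. Part of this stands. The primary endpoint is modelled by arm. The secondary endpoints (6MWT, PDQ-39, accelerometer) are not placed under the increaser comparison. A reader might infer that no randomised comparison of the additional measures is intended; the article does not say so, and its silence is not evidence. What does not stand is the idea that the contrast is merely a detail left out. The article names its comparison groups and its purpose, and that statement can be judged as it is.

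Three other strong readings are tempting and are not supported.

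- **That the contrast will show a benefit whatever the truth.** At ρ = 0 there is no bias, and at 0.05 the false-benefit rate is about 15%. Adjustment for baseline prognosis could lower ρ, though not the part that arises from the disease course after randomisation.
- **That a harm through falls will be hidden.** Falls share the section with the increaser comparison, but no sentence says they will be analysed that way. The Discussion says: "Safety is also an issue, because physical activity may theoretically predispose patients to falls". Patients who fall may cut back and so count as non-increasers, but more activity also means more exposure. If falls were analysed this way the result would be unreliable, in a direction that cannot be known in advance.
- **That bone density is distorted too.** Table 2 schedules DXA at baseline only, so there is no follow-up value to compare.

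**Conclusion.** The concern holds as a conditional statement. The planned comparison groups patients by a post-randomisation outcome, serves a causal aim, and is open to a bias whose mechanism the article itself describes. A correlation of 0.10 would raise the false-favourable rate from 2.5% to about 45%, and 0.20 would raise it to about 96%, with spurious differences of 0.16 and 0.32 SD. These figures rest on assumed values of ρ, half the patients being increasers, 527 analysable patients and an unadjusted contrast; a 30% share changes them little. The measures affected are motor progression, mobility, sleep, mood, fatigue, cognition and the Åstrand-Ryhming fitness test. The trial's main conclusion on activity level is untouched, so this is a point that should be fixed and not one that undermines the trial.

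**What to change.** In Additional measures, state that these measures, falls and adverse events are compared primarily by randomised arm, adjusted for the baseline value where one is collected. Keep the comparison of increasers with non-increasers only as an exploratory analysis, label it explicitly as non-causal, and define in advance what counts as an increase (which instrument, which visits, what threshold).

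The cost is wording and routine analysis, with no new data. The trade-off is that the by-arm contrasts estimate the effect of being offered the programme, not of achieved activity, and will be smaller than the increaser contrasts. That is the question the randomisation can answer.

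### The UPDRS motor section and peg-board test are labelled disease progression, but with no assessment after the programme they show only current motor severity

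*Protocol article*

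**What the plan says.** The protocol article describes the same motor measures in different ways.

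- **Methods, Additional measures:** the construct is progression: "Disease progression (UPDRS motor section [39]; 9-hole peg board test[40". The section opens by saying that patients whose activity rose will be compared with those who did not manage this, in order to study health consequences.
- **Table 2, Health Effects:** the UPDRS appears as "UPDRS III, motor function". The peg-board test is listed in the same block by test name only. Both are marked at baseline, 12 and 24 months.
- **Discussion:** the purpose is symptomatic: "We also want to see whether physical activity affords any symptomatic relief of PD". The next sentence links the endpoints to that aim: "To this end we have included a battery of additional endpoints (including quality of life) that measure possible health benefits for patients".
- **Abstract and Background:** the possibility of disease modification is raised as motivation. Physical activity may "perhaps even modify the course of PD", and animal work suggests that "physical activity may directly alter the neurodegenerative process".
- **Study Design and Table 1:** "Trial duration is two years", and the programme continues in the second year, with "12 coaching sessions to identify and focus on individual beliefs and aims to promote a physically active lifestyle" in the ParkFit arm.

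**The concern.** Progression and symptom severity are different constructs and support different claims. A better motor score while patients are exercising, or just as the programme ends, can arise because exercise relieves symptoms, because medication changed differently, or because the disease advanced more slowly. Only the last is an effect on progression. An outcome that carries the progression label in advance, in an article that raises disease modification in its Abstract and Background, invites a favourable score to be read as slower disease. The design as described cannot support that reading. The stated comparison by achieved activity makes it less secure still, because the groups are formed after randomisation by something that progression itself influences.

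**Working it through.** The plan gives no figure for this point, so there is none to reproduce. The check is whether the schedule and comparison can identify progression.

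**Inputs**

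1. Motor visits (Table 2): baseline, 12 and 24 months. No later visit, withdrawal period or delayed-start arm is described.
2. Programme (Table 1): ParkFit has 16 coaching and up to 19 physical therapy sessions in year 1 (16 + 19 = 35), and 12 and up to 23 in year 2 (12 + 23 = 35). ParkSafe has up to 35 physical therapy sessions in each year. Month 12 is therefore mid-programme and month 24 is its end.
3. Treatment: the exclusion criteria remove patients without a sustained response to dopaminergic therapy, so the population is essentially treated. This is an inference. Table 2 marks PD medication as collected at all five time points.

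**What a score difference contains**

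Write D(t) for the difference between two groups at month t, with positive values meaning better motor scores. Assume the parts add:

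D(t) = S(t) + M(t) + P(t)

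Here S is the symptomatic effect of current activity, M the effect of any difference in medication, and P the effect of any difference in progression. The visits give two values, D(12) and D(24), against six unknowns. Even if M were set to zero, two values would face four unknowns.

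Four patterns show the consequence. The symbol d is arbitrary, since the article gives no UPDRS or peg-board figure.

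| Pattern | Truth at months 12, 24 | D(12) | D(24) | D(24) − D(12) |
|---|---|---|---|---|
| A: constant symptomatic benefit | S = d, d; P = 0, 0 | d | d | 0 |
| B: symptomatic benefit that builds | S = d, 2d; P = 0, 0 | d | 2d | d |
| C: slower progression only | S = 0, 0; P = d, 2d | d | 2d | d |
| D: slower progression, less medication | P = d, 2d; M = −d, −2d | 0 | 0 | 0 |

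In A, all of d would count as slowed progression under the label although the true effect on progression is zero. B and C produce identical data, so the change from month 12 to 24 does not separate them. D shows the opposite error: a real effect on progression that leaves no difference in score. These patterns show that the components cannot be told apart. They do not estimate a size.

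**What the stated comparison adds**

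In a comparison of patients who did and did not raise their activity, P can differ even if activity has no effect at all, because patients whose disease advances more slowly find it easier to become more active. Comparing the randomised arms removes this selection. It does not separate S from P.

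**The case against.** The strongest reply is that this is a matter of one label. The stated objective is a lasting rise in activity, with a search for possible health benefits and risks. The two tests are neither the primary endpoint nor among the listed secondary measures. The remarks on disease modification are hedged background about physical activity in general. Table 2 and the Discussion already give the modest reading, and the article's conclusion also speaks of symptomatic effects. All of this stands, and it limits the weight. It does not make the progression label correct.

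Several stronger readings are tempting, and the documents do not support them.

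- A reader might infer that the trial plans to claim slowed progression. No such hypothesis or reporting intention is stated; misreading is a risk, not a plan.
- A reader might infer that medication is known to vary. Table 2 shows only that it is recorded.
- A reader might infer that both follow-up tests fall in mid-programme. That is so for month 12; month 24 is the end.
- A reader might count the medication state at testing, or adjustment for medication, as missing. Such detail commonly sits in the full protocol or analysis plan, which are not shown. Testing in a fixed medication state would in any case leave the symptomatic effect of activity in the score.
- A reader might expect a contrast of month 12 with month 24 to settle the matter. Patterns B and C show that it cannot.

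**Conclusion.** The point holds as one of labelling and interpretation, with minor to moderate weight. The article calls the UPDRS motor section and the peg-board test measures of progression in one place, and describes the UPDRS as motor function and the additional endpoints as symptomatic in others. With tests only at baseline, mid-programme and end of programme, a difference in score is a difference in current motor severity. The comparison by achieved activity brings in reverse causation as well.

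The conclusion rests on the schedule in Table 2 being complete for these tests and on the population being essentially treated, which is inferred from the exclusion criteria. The second is not essential: in untreated patients a symptomatic effect of activity would still be mixed with progression. The primary endpoint and the listed secondary measures are unaffected.

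**What to change.** 1. In Additional measures, replace the progression label with motor function for the UPDRS III, as in Table 2, and dexterity for the peg-board test.
2. State that no effect on disease progression will be inferred from these measures.
3. Report both primarily by randomised arm, next to the between-arm difference in PD medication over the same period.
4. Keep the comparison of patients who did and did not raise their activity as exploratory, and note that slower progression may be a cause of the rise.
5. Optionally show the change from month 12 to 24 separately, as description only. Even diverging arms would be no more than compatible with slower progression.

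The cost is wording, one extra table from data already scheduled for collection, and a more modest claim. No visit or measurement is added.
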